| Duration of study:        | Duration of study for each subject depends on the time point of symptom onset (see "Visit schedule") and may be maximally 16 weeks.                                                                                                                                                                                                                                                                                                                                                                                                                                                                                                                                                                                                                                                                                                                                                                                                                                                                                                                                                                |
| Number of participants:   | 
Expected number of subjects to be assessed for eligibility (at V1): n=300
 
Expected number of subjects to be allocated to trial/randomised: n=300
 
Expected number of subjects to enter the treatment phase (upon experiencing symptoms) and complete V2 and the study: n=200
 
Expected number of subjects to be analysed: n=200
 
Depending on the percentage of subjects from those randomized at V1 who actually develop symptoms during the study period, the envisaged number of 300 recruited subjects may deviate from the final number of subjects needed.
 
For reasons of practicability/logistics of recruitment, the targeted number of 200 subjects with symptoms may be subject to deviations of maximally +/- 20 subjects.
                                                                                                                                                                                                                                                                                                                       |

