| Investigational product use:     | 
The verum spray should be applied every second hour up to 6 times daily, each 2 puffs (1 dose).
 
6 times per day with each time 2 puffs per occasion.
 
Depending on the timepoint of treatment onset, there may be less IP applied on the first day of use.
                                                                                                                                                                                                                                                                                                                                                                                                                                                                                                                                                                                                                                                                                                                                                                                                                                                                                                                                                                                                                                                                                                                                                                                                                                                                                                                                                                                                                                                                            |

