### 8.2 DURATION OF THE STUDY

The study duration for each subject is maximally 16 weeks.

The expected start date of this study is Q1 2018. The clinical phase of the study is expected to be completed by Q1 2019.

If the required number of subjects with cold symptoms would not be achieved in the winter season 2017/2018, the recruitment would be stopped between March and September 2018 and continued in the next winter season (2018/2019).

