### 10.2 DOSAGE AND USE OF IP

The spray should be applied every second hour up to 6 times with each time 2 puffs (1 dose) per occasion. At V1, the subject will be instructed on the use and the application demonstrated.

[figure not shown]

Figure 2: Application of spray

Depending on the timepoint of treatment onset, there may be less IP applied on the first day of use.

The IP use should start when following conditions have been fulfilled:

- answering "Yes" to either of the questions in the subject diary: "Do you think/feel you have a cold?" or "Do you think/feel you are coming down with a cold (might be having first signs of cold)?"
- Jackson score of at least 1 (mild = sensible, but not disturbing or irritating) for any symptom except headache

The IP should be used until 2 days after the subject is symptom free (=answering "No" to the question "Do you think that you are still sick with this respiratory infection?" for 2 days in a row), but not longer than 12 days in total.

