### **12.3 VISIT 3 (V3, FINAL), 16 +/-4 DAYS AFTER SYMPTOM START**

- Questioning and documentation of possible occurrence of AEs/device deficiencies
- Questioning and documentation of new or changed concurrent treatment
- Return and control of the subject diary by a study team member (except investigator)
- Return of IP (verum group) and accountability
- Physical examination
- Measurement of blood pressure and pulse rate

- Global evaluation of efficacy by subjects (4-point categorical scale)
- Global evaluation of safety and tolerability by subjects (4-point categorical scale)

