## **12.9 ASSESSMENT OF FURTHER PARAMETERS**

### **12.9.1 IP usage**

Evaluation of IP usage (verum group) will be performed during statistical evaluation at study end, based on the return and documentation of unused investigational product (per vial weight for spray and item counting for capsules) as compared to study duration.

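### IP usage is compared with study duration, which includes the wait before any cold, so the measure mainly reflects onset time and cold length

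*Protocol*

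**What the plan says.** Section 12.9.1 bases IP usage on returned product, "per vial weight for spray and item counting for capsules) as compared to study duration". Section 7.3 lists IP usage in the verum group as the only further parameter.

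Section 8.2 states: "The study duration for each subject is maximally 16 weeks". The synopsis adds: "Duration of study for each subject depends on the time point of symptom onset".

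The spray is handed out at V1 (section 12.1) but is not used from then on. Section 10.2 ties the start to the cold criteria: "The IP use should start when following conditions have been fulfilled". It also sets the end: "The IP should be used until 2 days after the subject is symptom free", "but not longer than 12 days in total". A subject with a cold has the final visit "16 +/-4 DAYS AFTER SYMPTOM START" (section 12.3). The 16-week termination visit is for subjects who never had symptoms (section 12.4).

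The only product described is a 20 ml spray bottle (section 10.1), and section 10.4 plans accountability by vial weight. The diary records IP use each evening during the cold (section 12.7.1).

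**The concern.** The period named in 12.9.1 is not the period in which the spray is meant to be used. It adds the symptom-free days before the cold and the days between stopping the spray and V3. Two subjects who follow section 10.2 equally well would then get different usage values because one caught a cold in week 1 and the other in week 8. A subject whose cold was short, and who rightly stopped early, would read lower again. The result would be hard to interpret as a description of exposure or adherence.

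The reference to capsules, which this trial does not have, suggests that the sentence was carried over from another study.

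**Working it through.** The protocol states no usage percentage or target, so there is no figure to reproduce. The check is what the stated comparison gives for a subject who follows section 10.2 exactly.

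Inputs:
- Longest use: 12 days (section 10.2).
- Longest study duration: 16 weeks = 16 × 7 = 112 days (section 8.2).
- Final visit: day 16 after symptom start, window day 12 to day 20 (section 12.3).
- Onset day d, counted from V1: not given, so assumed and varied from 0 to 96. First use is taken to fall on the day of onset.

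Formula: ratio = days of IP use / (d + 16). At a constant number of doses per day the dose ratio is the same. For example, at 6 a day, (12 × 6)/(112 × 6) = 72/672 = 10.7%.

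The last column takes a 7-day cold. Because use continues for 2 days after symptoms end, full adherence is then about 7 + 2 = 9 days.

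| Onset day d (assumed) | Days in study, d + 16 | Full 12-day use | Full use, 7-day cold (9 days) |
|---|---|---|---|
| 0 | 16 | 12/16 = 75.0% | 9/16 = 56.3% |
| 14 | 30 | 12/30 = 40.0% | 9/30 = 30.0% |
| 28 | 44 | 12/44 = 27.3% | 9/44 = 20.5% |
| 56 | 72 | 12/72 = 16.7% | 9/72 = 12.5% |
| 96 | 112 | 12/112 = 10.7% | 9/112 = 8.0% |

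Identical 12-day use varies by a factor of 112/16 = 7 with onset time alone. For onset on day 0 the V3 window moves the ratio from 12/20 = 60% to 12/12 = 100%. Only onset on day 0 with V3 on day 12 and all 12 days used reaches 100%.

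If onset were uniform over days 0 to 96 (an assumption for illustration), full 12-day users would have a mean ratio of 24% and a median of 12/(48 + 16) = 19%. About 43% of them would fall at or below 17%.

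With the subject's own IP-use period as denominator, the same behaviour gives 12/12 or 9/9 = 100% whatever the onset day, leaving aside a shorter first day.

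**The case against.** The best defence is that study duration was loosely meant as treatment duration, that 12.9.1 gives no formula or percentage, and that the analysis plan promised in section 14.1.6 can set the calculation. The data for a sound measure are collected in any case: vial weights (section 10.4) and daily diary entries (section 12.7.1). It stands that the ratio above is one construction of the comparison and that nothing is lost for good. The wording is still not a mere gap. The protocol names the comparator, and elsewhere uses the same term for participation of up to 16 weeks. Section 8.2 gives no starting point, but the termination visit 16 weeks after V1 makes V1 the natural one.

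A reader might infer three stronger things, none of which the protocol supports:
- That full adherence would generally read as about 11–17%. The lower value needs a full 112 days in study, hence onset near day 96. The upper needs onset near week 8. Early onset gives far higher values and short colds lower ones.
- That every verum subject would look non-adherent. No threshold is stated, so nobody is classified.
- That the VCAS would be distorted. Sections 14.1.3 and 16.3 base it on major violations assessed at blind data review and do not name IP usage. A reviewer could judge use directly against section 10.2.

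**Conclusion.** The point holds: 12.9.1 names the wrong period. Taken literally, the measure varies about sevenfold with onset time under identical full use, from 75% down to 10.7% with V3 on day 16, and falls further for short colds. These values rest on assumed onset days and on reading the comparison as a ratio of days; no single range is typical.

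The consequences are limited. IP usage is descriptive, concerns one arm and feeds no efficacy endpoint in a pilot that disclaims confirmatory testing. It would matter more if the measure were used to decide major violations. Verum subjects with late or short colds would then be the ones marked down, with no matching check in the control arm. That is a possibility to close off, not something the protocol provides for. The capsule clause is a plain error on any reading.

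**What to change.** In 12.9.1, replace study duration with the subject's own IP-use period: first IP use to the stop point already set in section 10.2, at most 12 days, allowing for a part first day. Take use as the difference between vial weight at dispensing and at return, and cross-check it against the daily diary record. Delete the capsule clause. Report verum subjects who never had a cold as not applicable, since they have no such period.

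Two things are needed before expected use can be computed. The protocol gives no weight per dose, so one must be stated. The synopsis gives daily frequency as an upper limit in one sentence ("The verum spray should be applied every second hour up to 6 times daily, each 2 puffs (1 dose") and as a fixed six in the next, and section 10.2 gives the upper limit without saying per day. These statements must be reconciled by those responsible for the clinical content.

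The cost is small: one sentence, plus recording vial weight at dispensing and the weight per dose. Returned-product weight and diary entries are already planned. If usage is to inform the VCAS, that should be stated before the blind data review; otherwise nothing more is required.

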## **12.10 STUDY DISCONTINUATION**

Subjects may withdraw their consent and discontinue their participation in the clinical study at any time, without giving a reason for discontinuation. The investigator may terminate the clinical investigation for single subjects. Further, the sponsor has the right to terminate this clinical investigation.

### **12.10.1 Withdrawal of Subjects**

Reasons for subject's withdrawal may be for example:

- Serious adverse event (SAE)
- Intolerance of the investigational product
- Required additional therapy due to other complaints, which could influence the safety of the subject or the results of the study
- Clinically significant illness or intake of concurrent medication according to exclusion criteria, which could influence the results of the study
- Subject is not compliant with study requirements (according to investigator judgement)
- Withdrawal of informed consent
- Subjects in the study once the number of treated subjects has been completed

Reason, time and specific details of a subject's withdrawal are documented in the CRF. Each subject who terminates the study prematurely will be asked to undergo the final visit (corresponding to Visit 3) to be documented in the CRF.

If possible, the IP should be returned by the subject. Subjects who discontinue due to safety reasons should, whenever possible, be seen and assessed by the investigator and be medically treated as appropriate.

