### 7.1 EFFICACY PARAMETERS

Main endpoints:

Evaluation of various assessments of common cold symptoms by the observed magnitude of treatment effects:

- Sore Throat Scale
- Irritated Throat Scale
- Jackson scale – total score, local symptoms, systemic symptoms, 2-item score (sore throat & malaise)
- WURSS-21 QoL subscore
- Percentage of subjects with prevention of cold outburst

Further endpoints [SEP]

- Duration of common cold symptoms
- Use of concomitant treatment / remedies
- Global evaluation of efficacy by subjects at study end

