## 11 CONCURRENT TREATMENT

The subjects report the concurrent treatment (e.g. other medical devices, medication, any natural health products including food supplements etc.) to the investigator at the first visit. The investigator documents the following information in the CRFs: substance (only for treatment), dosage (only for treatment), start and duration, reason. Subjects will also be advised to inform the investigators of any treatment performed throughout the clinical investigation period.

During the study, the use of any concurrent treatment according to exclusion criteria is not allowed:

- Influenza vaccination within the last 3 months
- Regular use of products that may influence the study outcome (e.g. immune suppressants/immune stimulants including natural health products, analgesics/anti-rheumatics, anti-phlogistics, antitussives/expectorants, mouth or throat therapeutics, decongestants, antibiotics, anti-histaminergic drugs, nasal drops/spray) (except for the defined optional care)

At enrollment, the investigator informs the subjects that any concomitant treatment that could possibly influence the outcome of the study is not allowed, except for the defined optional care.

The following treatment is defined as optional care to be applied as needed during the common cold period:

- paracetamol (max. 2 g/day)
- ibuprofen (max. 400 mg/day)
- sea water nose drops or nose spray
- antibiotics (in case they are necessarily required).

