## **12.7 ASSESSMENT OF EFFICACY**

### **12.7.1 Subject Diary / Common cold assessment at V2**

In the daily subject diary, from V1 on, subjects will be asked to answer the questions "Do you think/feel you have a cold?" or "Do you think/feel you are coming down with a cold (might be having first signs of cold)?" (in the morning and in the evening).

From the first day they answer „Yes“ to either of the above questions, they will have to start filling out the cold diary instead, to:

- record their symptoms on the Jackson scale (twice daily, in the morning and in the evening)
- record their symptoms on the Sore Throat Scale (twice daily, in the morning and in the evening)
- record their symptoms on the Irritated Throat Scale (twice daily, in the morning and in the evening)
- fill out the Wisconsin Upper Respiratory Symptom Survey (WURSS-21) Quality of Life section (once daily, in the evening)
- answer the question "Do you think that you are still sick with this respiratory infection?" (once daily, in the evening)
- record the use of IP (verum group only; once daily, in the evening)
- record the use of any concomitant treatment / remedies (once daily, in the evening).

The cold diary should be filled out until 2 days after the subject is symptom free (=answering "No" to the question "Do you think that you are still sick with this respiratory infection?" for 2 days in a row).

The Jackson score (Jackson, 1958) is calculated by summing the following 8 symptom scores: sore throat, blocked nose, runny nose, cough and sneezing (local symptoms) as well as headache, malaise, and chilliness (systemic symptoms). Symptoms are assessed on a 4-point scale: 0 = none (symptom not present), 1 = mild (sensible, but not disturbing or irritating), 2 = moderate (symptoms sometimes disturbing/irritating), 3 = severe (symptoms disturbing/irritating most of the time).

The Sore Throat is a 0-10 Likert scale where 0=not sore and 10=very sore.

Irritated Throat Scale is a 0-10 Likert scale where 0=not irritated and 10=very irritated.

WURSS-21 (Barrett et al., 2009) is an evaluative illness-specific quality of life instrument with 21 items, designed to assess the negative impact of acute upper respiratory infection, presumed viral (the common cold). In this study, the QoL part of the WURSS-21 will be applied, from item 12 ("think clearly") to item 20 ("live your personal life").

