### **16.3 CIP DEVIATIONS**

No systematic or prospective deviations from the CIP are tolerated. CIP deviations will be evaluated during blind data review by the sponsor, the CRO, and the biometrician in order to define the study data sets.

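### Taking a barred cold remedy can end a subject's follow-up although remedy use is an endpoint, so the diary days lost may depend on severity and arm

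*Protocol*

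**What the plan says.** Protocol section 12.10.1 opens its list with "Reasons for subject's withdrawal may be for example". One entry is "Clinically significant illness or intake of concurrent medication according to exclusion criteria, which could influence the results of the study". Another is non-compliance in the investigator's judgement. A third is additional therapy for other complaints that could affect either safety or the results.

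Section 11 defines what is barred in two ways. Its bullet refers to "Regular use of products that may influence the study outcome" and names cough medicines, decongestants, throat products and nasal sprays among the examples, apart from optional care. Its next sentence is wider: "any concomitant treatment that could possibly influence the outcome of the study is not allowed, except for the defined optional care". Optional care is paracetamol, ibuprofen, sea water nose products and antibiotics where required.

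Section 7.1 lists "Use of concomitant treatment / remedies" as a further efficacy endpoint, and the cold diary in 12.7.1 asks each evening about any remedy used.

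For deviations, section 14.1.3 defines a VCAS that leaves out FAS subjects with major violations, and section 16.3 says that "CIP deviations will be evaluated during blind data review by the sponsor, the CRO, and the biometrician".

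**The concern.** Reaching for a decongestant or a cough medicine is something a subject does because the cold is bad. Here that same event is both an outcome to be compared between arms and a ground for ending the subject's participation. If participation ends during the cold, the diary stops, and the missing days belong to subjects selected by how ill they felt.

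The loss may also differ by arm. Section 10.6 leaves subjects unblinded, one arm holds a throat spray and the other holds nothing, and compliance with the IP is asked of one arm only.

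The trial's stated aim (sections 7.1 and 14.1.1) is to judge the assessments by the size of the treatment effect they show. Informative gaps in the diary bear on that quantity. Because the reasons are examples and rest partly on judgement, sites may also apply them differently.

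**Working it through.** The plan has no figure to reproduce. Section 14.1.5 sets 200 symptomatic subjects on practical grounds, and no withdrawal rate, SD or effect size is given. The check is a side-by-side reading, followed by an illustration.

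**1. What happens to the diary.** Section 12.10.1 asks early terminators for a final visit equivalent to Visit 3, and section 12.3 has the diary returned at Visit 3. The footnote to the flow chart (21.2) gives early terminators only a reduced terminal visit, again with return of the diary. The two visits differ in content, but the diary is handed in at both, and no section continues it.

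**2. What is then missing.** The diary carries the Sore Throat, Irritated Throat and Jackson scales, the WURSS-21 QoL items and remedy use. Section 12.7.1 dates the end of the cold by two consecutive days on which the subject no longer feels sick, so a diary returned earlier leaves duration unobserved. Section 14.1.4 allows no replacement after Visit 2.

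**3. When the event would come to light.** After onset the scheduled contacts are Visit 2 (days 1 to 3) and Visit 3 (16 − 4 = 12 to 16 + 4 = 20 days). The gap is 12 − 3 = 9 to 20 − 1 = 19 days. The monthly calls fall before Visit 2. A remedy taken after Visit 2 is therefore known before Visit 3 only if the subject reports it, as section 11 advises.
- Found at Visit 3, withdrawal costs little if the cold is over.
- Found at Visit 2, it costs most of the course. As a rough guide, section 5 cites 6.5 symptomatic days on placebo in a challenge study. Stopping at day 3 or day 1 loses 6.5 − 3 = 3.5 or 6.5 − 1 = 5.5 of those days, that is 54% or 85%.

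**4. What the analysis sets keep.** The FAS needs one data point after onset and, in the verum group, one dose. Days before withdrawal stay in. The subject is absent altogether only from the VCAS, and only if the event counts as a major violation.

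**5. Illustration of size (all rates assumed).** Take a normal severity score with SD 1 and 100 subjects per arm. If the worst fraction q of an arm is lost, its mean falls by m(q) = φ(z at 1 − q)/(1 − q): m(0.05) = 0.109, m(0.10) = 0.195, m(0.15) = 0.274. The shift against the IP is m(control) − m(verum). Simulated trials (3000 per case, Mann-Whitney U test, true effect 0.40 SD, withdrawn subjects left out entirely) used a correlation of 0.5 and then 1.0 between severity and withdrawal.

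| Lost, verum / control | Shift from formula (SD) | Mean estimate, correlation 0.5 to 1.0 | Power |
|---|---|---|---|
| none | 0 | 0.40 | 78% to 79% |
| 5% / 5% | 0 | 0.40 | 78% to 82% |
| 5% / 10% | 0.086 against IP | 0.36 to 0.31 | 68% to 67% |
| 5% / 15% | 0.166 against IP | 0.32 to 0.23 | 57% to 44% |
| 10% / 5% | 0.086 in favour of IP | 0.44 to 0.49 | 86% to 95% |

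With no true effect and correlation 1.0, the rejection rate rises from about 5% to 9% (5% / 10%) or 22% (5% / 15%). For scale, 100 per arm detects (1.960 + 0.842) × √(2/100) = 0.396 SD with 80% power at a two-sided 5% level.

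The table removes whole subjects, which the FAS does not do. It shows how the shift depends on the difference in loss between arms, including its sign; it does not estimate the effect in this trial.

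**The case against.** The strongest reply is that the trigger is narrow and the consequence limited. The list gives examples and does not require removal. The entry in 12.10.1 refers back to the exclusion criteria, where the wording is regular use. Optional care can be used and recorded without any breach. The scheduled checks would miss most remedy use until Visit 3. Data before withdrawal remain in the FAS, and the study is exploratory (14.1.2). All of this stands, and it limits both the frequency and the size of the loss.

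A reader might go further and infer that controls, having no spray, would lose more of their worst colds, so that a true effect would be hidden. The documents do not support that direction. It is plausible for remedy use, but compliance with the IP (section 9.2) and intolerance of the IP (12.10.1) concern the verum group only and could push the loss the other way. Nor can a reader conclude that the ranking of the assessments is distorted: the diary scales would lose the same days together, and no change in their relative performance has been shown.

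It may also be said that the SAP, which is not at hand, can deal with missing diary days. It can choose a method for them, but it cannot recover days that were never collected. That part of the objection fails, because the stopping of data collection is fixed in the protocol.

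**Conclusion.** The point holds in a limited form. The protocol lets an outcome-related event, or judged non-compliance, end collection of the diary on which most of the efficacy endpoints rest. The resulting gaps can depend on severity and on arm. The loss is partial in the FAS. Its size and direction cannot be worked out from the document, and the SD figures above rest on assumed rates, a normal score and removal of whole subjects. It would be wrong to read this as a demonstrated bias against the IP or in its favour. It is a cheap improvement that prevents avoidable informative missing data, not a flaw that invalidates the design.

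**What to change.** In section 12.10.1, stop using three things as reasons to end follow-up: intake of non-permitted medication, non-compliance, and additional therapy where the only ground is possible influence on the results. State that such subjects continue the cold diary to its normal end and attend Visit 3. Record the remedy both as endpoint data and as a CIP deviation, and decide on the VCAS at the blind review in 16.3. FAS membership needs no change.

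Leave the consent, safety and enrolment-cap reasons as they are, as well as the rules on which treatments are permitted. Report withdrawals by arm and reason.

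Two pairs of statements need reconciling: regular use against any outcome-influencing treatment in section 11, and the final visit in 12.10.1 against the reduced terminal visit in the footnote to 21.2.

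The cost is protocol wording and a site instruction. A small downside is that some FAS data will come from subjects who used non-permitted remedies; the VCAS can isolate these. The change does not remove selection from the VCAS itself, so the FAS result should be read beside it.
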